##### Pain catastrophizing scale (PCS)

The PCS comprises 13 items divided into three subscales (rumination, magnification, and helplessness) measuring catastrophizing thoughts [36]. Total PCS scores range from 0 to 52; a score of 20 represents a moderate to high risk for the development of chronicity [56].

##### Pain self-efficacy questionnaire (PSEQ)

The PSEQ is a 10-item questionnaire to assess a person’s confidence in their ability to manage pain and perform activities while in pain [37]. PSEQ scores range from 0 to 49; scores < 17 represent a low score preventing the modification and maintenance of behavioral change [37].

#### Feasibility and acceptability

A Program Feasibility Evaluation Logbook will make it possible to collect program feasibility data (Table 3) [58]. The Program Feasibility Evaluation Logbook will detail information on the program components that need to be delivered in each session, the pain self-management strategies applied by participants between sessions, the appropriateness of the physical environment in which the program is delivered, the time dedicated to adequately deliver the program and answer patient questions, and the challenges faced when providing the program.

**Table 3 Tab3:** Variables to assess the feasibility of the intervention and the research methods

Variables	Indicators
*Intervention feasibility*	
1- The possibility to deliver the intervention as planned 2- Participants adhering to the intervention	- Provision of ≥80% of planned components of each in-presence session and of the overall intervention [59].
	- Session duration (sessions 1 to 6: 15 min).
	- Challenges faced during session delivery.
	- Attendance to ≥80% of sessions by participants [59].
	- Involvement in intervention activities and implementation of recommended self-management ≥80% behaviors by participants [59].
*Research methods feasibility*	
1- Adequacy of the sampling pool and recruitment time 2- Ease of screening 3- The possibility of applying randomization procedures as planned 4- Attrition rate in experimental and control groups 5- Ease of data collection procedures	- Obtaining consent from ≥80% of patients approached to participate in the study.
	- Percentage of eligible patients who were included in the study. - Patient’s reasons for refusal to participate in the study.
	- Difficulties in obtaining patients’ consent.
	- Recruiting study sample (i.e., 50 participants) in ≤9 months [31].
	- The time required to screen participants relative to recruitment.
	- The time required to obtain consent and baseline data relative to recruitment.
	- Eligibility criteria not limiting the pool of participants by ≥50% [32].
	- Reasons for ineligibility.
	- Difficulties when applying the randomization procedures.
	- Patient acceptance to randomization, either to the treatment or control group ≥80% of the time [32].
	- Attrition rate in experimental and control groups, i.e., ≤ 20% [60].
	- Percentage of questionnaires completed in full.
	- Pattern and rates of non-answered questions at each time measure.
	- Mean time required to complete the outcome questionnaires.
	- Mean time period between expected dates for questionnaire completion and actual completion.
	- Recall rates (telephone calls or emails) for questionnaire completion.

Gathering data on the intervention components provided and on challenges in the application of the intervention activities, in the selected mode, and the selected dose, will also demonstrate the fidelity with which the intervention can be delivered [32].

A Research Methods Feasibility Form will assess methodological research criteria parameters, established according to recognized guidelines [32, 58, 59] and data from iPACT-E-Trauma’s preliminary testing [29, 31] (Table 3). This form will monitor: (1) adequacy of the sampling pool and recruitment time, (2) ease with which participants are screened, (3) possibility of applying randomization procedures as planned, (4) attrition rate in experimental and control groups, and 5) ease of data collection (Table 2).

The Treatment Acceptability and Preference (TAP) Questionnaire [59] will be used to evaluate intervention feasibility after its completion. The TAP includes four attributes (i.e., perceived effectiveness, appropriateness, suitability, and convenience) assessed on a 5-point descriptive scale. Patients will be invited to rate intervention’s features based on these attributes. An open-ended questions was added at the end of the questionnaire to gather input on the modifications required to improve intervention acceptability. Reliability, construct validity and discriminant validity of the TAP Questionnaire have been established with a population receiving self-management intervention [60]. The intervention uptake (i.e., the implementation of self-management behaviors and the reduction of opioids as recommended), the enrollment rate, with the reasons for refusing to participate, and the attrition rate, with the reasons for dropping out, will be used to further determine TOPP-Trauma acceptability [32] for patients at high-risk of chronic opioid consumption.

### Variables and Measurement Tools

#### Morphine equivalent dose/day

Opioids taken by participants will be measured by calculating the total morphine equivalent dose (MED) per 24 h, as recommended for studies on the consumption of opioids, using the appropriate conversion methods [61, 62]. Participants will be asked to self-report their opioid use for the last three days and the day associated with the highest MED will be retained. The MED/day will be measured at 6 weeks after the beginning of TOPP-Trauma, since some studies found that a great proportion of trauma patients do not use opioids beyond this period of time [22], as well as at 12 weeks after initiating the intervention. The medical file will be consulted to determine the highest MED over three days before participant randomization, as part of baseline assessment. A pharmacist, blinded to patient allocation, will compute the MED per day.

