### Eligibility Criteria

The inclusion criteria will be: 1) having suffered a traumatic injury (e.g., fractures to the extremity and the spine, thoraco-abdominal injuries), 2) at least 18 years of age, 3) able to read and speak French or English, 4) ≥ 2 doses/day of opioids during the three previous days, 5) at least one risk factor for chronic consumption, and 6) discharged directly from hospital to home. The risk factors for chronic consumption are: a) annual income ≤ $40,000 [13, 15], b) ISS ≥ 12 [15], c) pre-injury use of opioid or substance abuse [Alcohol, Smoking and Substance Involvement Screening Test – version 3.0 ≥ 11 for alcohol and ≥ 4 for other substances [2, 12–14, 34], d) anxiety or depression symptoms [scores ≥11 on the Hospital Anxiety and Depression Scale [2, 16, 35]; e) pain catastrophizing [score ≥ 20 on the Pain Catastrophizing Scale [2, 16, 36], and f) pain self-efficacy [score < 17 on the Pain Self-Efficacy Questionnaire [4, 37]. The exclusion criterion will be patients with cognitive impairment [i.e., moderate-severe traumatic brain injury (TBI) – Glasgow Coma Scale score < 13/15 [38], dementia and severe psychiatric disorder] affecting the capacity to participate in the study.

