#### Co-analgesia

Non-opioid analgesics will be measured by asking participants to self-report, at the various follow-up time points, on whether they used ≥2 doses of each class of analgesic, for at least one day over the last three days. The medical record will be reviewed to document the consumption of non-opioid analgesics for the 3 days before randomization. Data on non-opioid analgesics delivered by community pharmacies will also be collected at 6 and 12 weeks after beginning TOPP-Trauma.

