### Data Collection

#### Procedure

At enrollment, RAs will complete the Injury Profile Form and Research Methods Feasibility Form. They will also document opioid and non-opioid consumption over the last 3 days and distribute the BPI. During program delivery, the trauma nurse and the pharmacist will record information on the feasibility of the program and the attrition rate via the Program Feasibility Evaluation Logbook and the Research Methods Feasibility Data Form. A RA will contact participants in the experimental and control groups over the phone, or meet them at the outpatient clinic, to document their opioid and non-opioid consumption and complete the BPI questionnaire, at 6 and 12 weeks after randomization. They will also contact participants’ community pharmacies to obtain information on opioid and non-opioid delivery at both time periods.

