#### Potential efficacy of the program

All outcome data will be analyzed via an intent-to-treat approach. Mean values will be calculated to determine the direction and amplitude of the differences within and between groups on the outcome measures over time. The percentage of opioid-free participants, of participants taking ≥2 doses per day of each class of non-opioid analgesic, and of participants with mild pain intensity and pain interference with activities (i.e., < 4 of a 0–10 Numerical Rating Scale) [64] will be computed. Data will be analyzed at baseline, 6 weeks and 12 weeks.

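### Baseline opioid and non-opioid use is read from the hospital file but follow-up use is self-reported, so the planned within-group change from baseline mixes a change of source with a change in use

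*Protocol article*

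**What the plan says.** The section on morphine equivalent dose per day sets two sources. For baseline: "The medical file will be consulted to determine the highest MED over three days before participant randomization, as part of baseline assessment". For follow-up: "Participants will be asked to self-report their opioid use for the last three days and the day associated with the highest MED will be retained". In the same section, computing the MED is assigned to a pharmacist who does not know the allocation.

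The Co-analgesia section makes the same split. For baseline: "The medical record will be reviewed to document the consumption of non-opioid analgesics for the 3 days before randomization". After that: "Non-opioid analgesics will be measured by asking participants to self-report, at the various follow-up time points".

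Follow-up reports are collected remotely or in clinic: "A RA will contact participants in the experimental and control groups over the phone, or meet them at the outpatient clinic". Participants must have been "discharged directly from hospital to home", so follow-up use is use at home.

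The section on potential efficacy states: "Mean values will be calculated to determine the direction and amplitude of the differences within and between groups on the outcome measures over time". It closes: "Data will be analyzed at baseline, 6 weeks and 12 weeks". The Discussion (Study contributions) then presents within- and between-group differences as adequately estimated for planning a full trial.

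Study limitations acknowledges social desirability bias in the 6- and 12-week self-reports and relies on community pharmacy delivery records to counter it. It does not mention that baseline comes from a different source.

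**The concern.** A within-group change is a change in use only if use is ascertained in the same way at both ends. Here one end is a hospital record of inpatient medication and the other is a patient's account of what was taken at home. Any systematic difference between the two goes into the change alongside the true change.

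The protocol itself expects a bias at the follow-up end. For opioids, social desirability would lower the reported dose, so both arms would appear to improve more than they did. What is at stake is the use of the within-group figures. If they go into the design of a full trial as estimates of how much opioid use falls, or of what the program achieves, part of the figure may come from the change of source.

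**Working it through.** **Step 1: sources side by side.**

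| Measure | Baseline | 6 and 12 weeks |
|---|---|---|
| MED/day | Medical file, three days, highest day | Self-report, three days, highest day |
| Non-opioid analgesics | Medical record, three days | Self-report: at least 2 doses of a class on at least one of three days |
| Community pharmacy records | None | Quantity delivered, opioid and non-opioid |

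For MED the window, the choice of the highest day and the computation match. The mismatch is one of source and setting. No row has a single source spanning baseline and follow-up. Pharmacy records measure delivery over several weeks, not intake on the highest of three days, so they cannot stand in for either end of the MED change.

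**Step 2: effect on the within-group change in MED.** The protocol gives no figure to reproduce, so this is an illustration. Let *r* be the true fractional fall in use and *u* the fraction of follow-up use that recall misses. Assume that the chart is accurate at baseline. The documents state none of these.

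Apparent fall = 1 − (1 − *r*)(1 − *u*); excess over the true fall = *u*(1 − *r*).

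| True fall *r* | *u* = 0 | 10% | 20% | 30% | 40% |
|---|---|---|---|---|---|
| 0% | 0% | 10% | 20% | 30% | 40% |
| 50% | 50% | 55% | 60% | 65% | 70% |
| 90% | 90% | 91% | 92% | 93% | 94% |

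With an assumed baseline of 60 mg/day and *u* = 30%:
- No true change: 60 × 0.30 = 18 mg/day of apparent fall that did not occur.
- True 50% fall: true follow-up 30, reported 21, excess 9 mg/day.
- True 90% fall: true follow-up 6, reported 4.2, excess 1.8 mg/day.

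The distortion shrinks as the true fall grows.

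**Step 3: effect on the between-arm contrast.** Assume a baseline of 60 in both arms and true follow-up of 20 (control) and 10 (experimental), a true difference of −10 mg/day.
- *u* = 20% in both arms: reported 16 and 8, difference −8. As a difference of changes: (8 − 60) − (16 − 60) = −8.
- *u* = 40% in both arms: reported 12 and 6, difference −6.
- *u* = 20% in control and 40% in experimental: reported 16 and 6, difference −10, because the two errors happen to offset.

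The charted baseline cancels each time. Misreporting at follow-up can move the contrast; the change of source from baseline cannot. Meanwhile the within-group fall in control, truly 40, would read 44 at *u* = 20% and 48 at *u* = 40%.

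**Step 4: non-opioids.** The outcome is a yes/no threshold, so the formula in Step 2 does not carry over. The later counseling sessions steer patients toward acetaminophen, so social desirability could raise reports rather than lower them. All that can be said is that the source differs, with the direction of any bias unknown.

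**The case against.** The strongest case on the other side is that this is a descriptive, unpowered pilot with a concurrent randomized control, so potential efficacy can be read between arms, where the switch does no harm. The inpatient chart is the natural baseline source. The protocol already concedes self-report bias and collects pharmacy records as a check. It also cites studies in which many trauma patients no longer use opioids after six weeks; true non-users have nothing to under-report, and a large true fall leaves little distortion. Natural recovery already prevents the within-group fall from being read as an intervention effect.

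Most of this stands and limits the point. It does not remove it, because the analysis section plans within-group differences that include baseline, the Discussion offers them as adequate estimates, and the pharmacy check does not reach baseline.

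A reader might go further and infer that the chart captures every dose, so that the whole self-report bias passes into the change. The documents say nothing about chart completeness, and the pharmacy records may expose some under-reporting. A reader might also attribute the claim of adequate estimation to the study objectives. The third objective only sets out to describe potential efficacy; the stronger claim is in the Discussion alone.

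**Conclusion.** The point holds in a limited form. The change from baseline to 6 or 12 weeks in MED/day and in non-opioid use cannot be read as change in use alone, because source and setting change with it. For MED the likely direction is an exaggerated fall, if follow-up under-reporting is the main error. The excess is *u*(1 − *r*) of the baseline value: with an assumed 30% missed, 30 percentage points if use did not change, but 3 points if it fell by 90%. The 18 mg/day figure needs unchanged use after the acute phase and should not be taken as the expected case.

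The point does not show that the randomized comparison is biased by the switch. It also does not show that non-opioid use is under-reported. It is an issue of interpretation that should be corrected, not a flaw in the design.

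**What to change.** In the section on potential efficacy, state that potential efficacy rests on the between-arm difference at 6 and at 12 weeks, adjusted for the charted baseline MED that is already collected. Keep any change from baseline as a description, labelled *charted inpatient dose versus self-reported home dose* (with a matching label for non-opioids), and say that it will not serve as an intervention-effect estimate for the full trial. Align the Discussion statement on adequate estimation with this. In Study limitations, add that baseline comes from a different source and that the pharmacy records do not cover it.

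A baseline self-report of the same three days, compared with the chart, would be an inexpensive optional addition, but the fix does not depend on it.

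The cost is wording and slightly more analysis work, with no new data. The within-group fall will carry less weight in the report. Adjustment does not remove self-report bias at follow-up, so the existing limitation still applies to the between-arm contrast.

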#### Opioid delivery by the community pharmacy

A registry will be used to document the quantity of opioids prepared by the community pharmacy at 6 and 12 weeks after initiating TOPP-Trauma. Community pharmacies will be contacted to gather information on opioids delivered following participant informed consent.

#### Co-analgesia

Non-opioid analgesics will be measured by asking participants to self-report, at the various follow-up time points, on whether they used ≥2 doses of each class of analgesic, for at least one day over the last three days. The medical record will be reviewed to document the consumption of non-opioid analgesics for the 3 days before randomization. Data on non-opioid analgesics delivered by community pharmacies will also be collected at 6 and 12 weeks after beginning TOPP-Trauma.

#### Pain and function

The Brief Pain Inventory (BPI) will be used to assess pain intensity and patient function. The BPI includes 11 items: 4 on pain intensity (now, average, worst, least) measured on a 0–10 NRS (0 = no pain; 10 = worst possible pain), and 7 on pain interference with daily living activities, assessed on a 0–10 NRS (0 = does not interfere; 10 = interferes completely) [63]. The BPI item “walking” was replaced by “mobility (ability to get around)” [55] because many trauma patients may be limited in their walking capacity. Moreover, three additional items (pain interference with self-care, recreational activities, and social activities), proposed in a modified version of the BPI [55], will be added to the Pain Interference with Daily Living Activities Subscale to obtain a broader-based sample of areas that could potentially be affected by pain. The worst pain intensity upon movement, on average in the last 7 days, and the worst score for pain interference with daily living activities during the same period, will be measured at 6 and 12 weeks. Baseline measures of pain intensity and interference will cover the previous 48 h.

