### Intervention

#### Control group

Participants randomized to the control group will receive the standard pain management intervention, consisting in non-opioid analgesics and opioids to control pain, as well as an educational pamphlet. The pamphlet will be provided to participants by the interventionist before hospital discharge, with no specific guided sessions, reflecting what is most commonly implemented in clinical practice. Furthermore, we hope to determine if patients receiving only an educational pamphlet are more likely to drop out than patients with follow-up. We also wish to explore if education at hospital discharge is sufficient to reduce long-term consumption of this type of analgesic.

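### Pain is recalled over 48 hours at baseline but over 7 days at 6 and 12 weeks, so planned pain contrasts with baseline mix real change with a change of measurement

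*Protocol article*

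**What the plan says.** All three definitions stand in the protocol article under Pain and function.

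- Intensity at 6 and 12 weeks: "The worst pain intensity upon movement, on average in the last 7 days".
- Interference at 6 and 12 weeks: "the worst score for pain interference with daily living activities during the same period, will be measured at 6 and 12 weeks".
- Baseline, for both: "Baseline measures of pain intensity and interference will cover the previous 48 h". No summary is given, so the text does not say whether the baseline score is worst or average, or whether it refers to movement.

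The section Potential efficacy of the program then treats baseline as one of three analysed time points: "Data will be analyzed at baseline, 6 weeks and 12 weeks". It plans two kinds of output for pain. The first is "Mean values will be calculated to determine the direction and amplitude of the differences within and between groups on the outcome measures over time". The second is the percentage "of participants with mild pain intensity and pain interference with activities", with mild meaning below 4 on the 0–10 scale. Table 2 shows the Brief Pain Inventory as a single row ticked at enrollment, 6 weeks and 12 weeks, with no recall window.

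**The concern.** A within-group change is interpretable only if the same quantity is measured at both ends. Here the recall window changes from 2 days to 7, and the summary is undefined at baseline and ambiguous for intensity at follow-up. A worst score tends to rise as the window lengthens, even in a patient whose pain is stable. An average does not. A fixed cut-off of 4 means something different under each definition.

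At stake are the reported change in pain from baseline within each arm and the baseline-to-follow-up comparison of the mild-pain percentages. A later analysis plan cannot repair this, because a 48-hour score cannot be recovered from a 7-day answer. It has to be settled in the questionnaire.

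**Working it through.** The protocol states no figure for this point, so there is nothing to reproduce. The check has two parts.

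**1. Windows side by side (protocol article)**

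| Outcome | Baseline | 6 and 12 weeks |
|---|---|---|
| Opioid dose per day | highest over 3 days | highest over 3 days |
| Non-opioid analgesics | 3 days | 3 days |
| Pain intensity | 48 h, summary not stated | 7 days, worst and average both named |
| Pain interference | 48 h, summary not stated | 7 days, worst |

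The window is matched for both drug-use outcomes and unmatched only for pain. No reason or adjustment is given, and the pain contrasts are not limited to same-window comparisons.

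**2. Possible size, with no true change**

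Every input here is an assumption, because the protocol gives no variability for pain. Daily scores are taken as independent and normal around the patient's own mean, with day-to-day SD s; 48 h is taken as 2 days.

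The expected maximum of k standard normal values is the integral of x·k·φ(x)·Φ(x)^(k−1):

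- k = 2: 0.564
- k = 7: 1.352
- difference: 1.352 − 0.564 = 0.788

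If both scores are worst scores, the artefact is +0.788·s. This gives 0.79 points for s = 1 and 1.58 points for s = 2.

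A simulation of 200,000 patients, with scores rounded and held to 0–10, true mean 4, between-patient SD 1.5 and s = 1.0, gives the following for each reading of the text:

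| Baseline (48 h) | Follow-up (7 days) | Mean | Apparent change | Share below 4 |
|---|---|---|---|---|
| worst | worst | 4.57 → 5.35 | +0.78 | 26.7% → 12.7% |
| worst | average | 4.57 → 4.01 | −0.56 | 26.7% → 48.1% |
| average | worst | 4.01 → 5.35 | +1.34 | 44.1% → 12.7% |
| average | average | 4.01 → 4.01 | 0.00 | 44.1% → 48.1% |

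The small shift in the last row's percentages comes from rounding and ties at exactly 4. With continuous scores it is 50% at both windows.

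Sensitivity:

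- For s from 0.5 to 2.0 at true mean 4, worst-to-worst runs from +0.39 to +1.55 points, and worst-to-average from −0.28 to −1.07.
- At true mean 5 and s = 1.0, the worst-to-worst share below 4 goes from 11.2% to 3.9%.

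For interference the follow-up score is explicitly the worst, so only the first and third rows apply and the artefact is upward in both. For intensity all four rows remain open.

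**The case against.** The strongest reply is that little depends on this. The pilot is about feasibility, its third aim concerns opioid consumption, and pain is an additional descriptive outcome. Both arms have the same windows at every visit, so between-group comparisons are like with like, and so is 6 against 12 weeks. A short window may be sensible for recently injured inpatients. All of this stands, except that the protocol gives no such reason for the short window and still lists within-group change and baseline among its analyses.

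The magnitude is also open to challenge. It assumes independent days and patients who recall a true maximum, and the shift in percentages depends on how close the mean lies to 4. Positive correlation between neighbouring days would shrink the artefact. This also stands, and the figures illustrate scale only.

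Three stronger readings are tempting, but the documents do not support them.

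- A reader might infer that follow-up pain is biased upward throughout. For intensity that needs both scores to be maxima, which the text does not say; the sign could reverse, or the mean shift could be about zero.
- A reader might infer that the pain change feeds the design of the full trial. The sentence under Study contributions about preparing for that trial concerns opioid consumption, whose windows are matched.
- A reader might look to Table 1 for ready-made 48-hour follow-up scores. Those are average scores, taken in counseling sessions that only the experimental arm attends.

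**Conclusion.** The point holds for contrasts of pain intensity and interference with baseline, and only for those. As written, the within-group pain changes and the movement of the below-4 percentages from baseline cannot be separated from the change of window and summary.

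For interference, if baseline is also a worst score, the expected artefact is about 0.8 day-to-day SD upward, or 0.8 to 1.6 points for an assumed SD of 1 to 2; it would make recovery look smaller than it is. For intensity neither size nor direction can be determined from the protocol. The consequence is modest, because the outcomes are descriptive and the between-arm comparisons are intact. It is still worth correcting, because one aim of the pilot is to show that its methods collect data that answer its questions.

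**What to change.** Define one summary for intensity (worst or average, and whether on movement) and one for interference, and use each unchanged at baseline, 6 weeks and 12 weeks. Replace the wording that names both worst and average. At 6 and 12 weeks, ask both items over the previous 48 hours, and base change from baseline and the below-4 percentages on those answers. The 7-day items may be kept as additional description.

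If the 7-day window is to remain the only one at follow-up, state why baseline is shorter, use baseline pain only to describe the groups, and limit pain contrasts to between-group comparisons at each visit and to 6 versus 12 weeks.

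The first option costs a slightly longer questionnaire at two visits or, if the 7-day items are dropped, a shorter picture of pain. The second costs no extra data collection but gives up change from baseline for pain. With matched window and summary, the artefact is zero by construction when there is no true change.
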